## Abstract

**Background:**

There are two primary surgical techniques to reconstruct the anterior cruciate ligament (ACL), transtibial (TT) technique and anteromedial portal (AMP) technique. Currently, there is no consensus which surgical technique elicits the best clinical and functional outcomes. MRI-derived measures of the signal intensity (SI) of the ACL graft have been described as an independent predictor of graft properties. The purpose of this study is to compare the MRI derived SI measurements of the ACL graft one year after ACL reconstruction, in order to compare the outcomes of both the AMP and TT ACL reconstruction technique.

**Methods/design:**

Thirty-six patients will be included in a randomized controlled trial. Patients who are admitted for primary unilateral ACL reconstruction will be included in the study. Exclusion criteria are a history of previous surgery on the ipsilateral knee, re-rupture of the ipsilateral ACL graft, associated ligamentous injuries or meniscal tear of the ipsilateral knee, unhealthy contralateral knee, contra-indications for MRI and a preference for one of the two surgical techniques and/or orthopaedic surgeon. Primary outcome is MRI Signal intensity ratio (SIR) of the ACL graft. Secondary outcome measures are the International Knee Documentation Committee (IKDC) Knee Examination Form,the Knee injury and Osteoarthritis Outcome Scores (KOOS) and the Anterior Cruciate Ligament OsteoArthritis Score (ACLOAS). Differences between MRI SIR assessment with the current MRI protocol (proton density weighted imaging protocol) and the additional T2*-weighted gradient-echo protocol will be assessed.

**Discussion:**

There is no consensus regarding the TT or AMP ACL reconstruction technique. SI measurements with MRI have been used in other clinical studies for evaluation of the ACL graft and maturation after ACL reconstruction compared to clinical and functional outcomes. This randomized controlled trial has been designed to compare the TT technique with the AMP technique with the use of MRI SI of the graft after ACL reconstruction.

**Trial registration:**

Netherlands Trial Registry NTR5410 (registered on August 24, 2015).

## Background

Rupture of the anterior cruciate ligament (ACL) is a frequently seen (sport) injury mostly induced by a non-contact deceleration motion. The risk of primary ACL rupture has been reported to occur in 1.5 to 1.7 % in healthy athletic population [1]. The ACL provides anterior-posterior and rotational stability to the knee joint. Initially, a rupture of the ACL leads to a synovial layer in the knee joint. The ends of the ruptured ACL tears will shrink and as a result of that, there is no healing process of the ACL. Long term consequences are chronic knee instability and osteoarthritis [2, 3].

There are several surgical techniques to reconstruct the ACL, which vary in graft type, number of bundles, method of fixation and tunnel position. More than 5000 ACL reconstructions are performed in The Netherlands each year [4]. The focus of ACL reconstruction is now changing toward the tunnel position of the ACL grafts since there is no established “gold-standard” technique for ACL reconstruction [5, 6]. The most frequently performed surgical technique is the transtibial (TT) drilling technique in which a femoral tunnel is drilled through the tibial tunnel. In this way, the femoral tunnel is placed non-anatomically relative to the native femoral ACL footprint [7]. Another surgical technique is the anteromedial portal (AMP) anatomic drilling technique which principle is based on restoring the native insertion site anatomy on both tibial and femoral side. The choice of drilling technique is depending on several factors such as surgeon experience, available equipment, patient age, skeletal maturity, body habitus, activity level and graft choice [5].

Robin et al. conducted a systematic review of the advantages and disadvantages of both reconstruction techniques based on 27 articles [5]. The main advantages of TT technique are single incision, isometric graft throughout knee range of motion and minimal tunnel and intercondylar notch impingement. However, disadvantages are that the tibial tunnel dictates the femoral tunnel, vertical and anterior graft placement, increased biomechanical demand during rehabilitation and TT requires notchplasty for visualization.

AMP technique leads to anatomic placement of femoral tunnel and independently tibial tunnel, anteroposterior stability, faster return to activity and useful for revision ACL reconstruction [5]. The main disadvantages of AMP are difficulty visualization in hyperflexion, posterior-wall blowout, technically demanding, limit fixation techniques due to short sockets, increased risk of injury to peroneal nerve and extension loss during stance phase [5].

Currently, there is no consensus which surgical technique elicits the best clinical outcomes. However, TT is the technique until now with long term follow-up results [5, 8].

Success of the ACL reconstruction can be measured by clinical, functional and patient-oriented outcome assessments include physical examination and patient-oriented questionnaires. However, these assessments are an indirect measure of the graft integrity and require large numbers of patients to detect differences between both operation techniques [9]. There is a need for a quantitative in vivo measurements method for the evaluation of the biomechanical performance and integrity of the ACL graft.

Magnetic resonance imaging (MRI) is the most effective and accurate technique for the quantitative in vivo assessment of the ACL with a sensitivity and specificity of more than 90 % [10]. Most common used MRI sequences for assessment of the ACL are turbo spin echo (TSE) sequences such as proton density weighted imaging (PDWI). Normally, an intact ACL appears in all planes as a low-signal linear band with an orientation at least as steep as the intercondylar roof. Between the fibers of the ACL there can be fat or fluid and therefore the ACL is not completely black on PDWI images. Primary signs of ACL rupture are increased signal on MRI, fiber discontinuity, abnormal orientation and undetectable fibers [11].

MRI-derived measures of the signal intensity (SI) of the ACL graft have been described as an independent predictor of graft properties [9]. Lower SI indicates low water and fat content and thus better maturity of the graft. MRI assessment with PDWI fails to correlate SI with actual graft function. A more promising technique is T2*-weighted gradient-echo MRI imaging which has been reported as a useful imaging modality to assess graft integrity [12]. The signal intensity ratio (SIR) can be calculated by:$$ \mathrm{SIR} = \mathrm{A}\mathrm{C}\mathrm{L}\ \mathrm{graft}\ \mathrm{intensity}\ /\ \mathrm{posterior}\ \mathrm{cruciate}\ \mathrm{ligament}\ \left(\mathrm{P}\mathrm{C}\mathrm{L}\right)\ \mathrm{intensity}. $$

The purpose of this study is to compare the MRI derived SI measurements of the ACL graft one year after ACL reconstruction, in order to compare the graft integrity of both the AMP and TT ACL reconstruction technique. The anatomical AMP reconstruction technique restores rotational stability. Non-anatomical TT reconstruction technique restores anterior/posterior stability but lesser rotational stability [5]. It is hypothesized that the AMP technique will result in significantly lower MRI signal intensity one year postoperatively and thereby better graft maturity due to the better rotational stability compared to the TT technique. The results of this study may clarify which surgical technique will reveal the best clinical, functional and quantitative MRI outcomes. This paper reports on the study design of the TRANSIG (TRanstibial vs ANteromedial portal technique SIGnal Intensity) trial.

## Methods/design

### Study design

The study design is a randomized controlled trial: patients will be randomly allocated to undergo ACL reconstruction by means of the TT and AMP drilling technique. The study will be conducted at the department of Orthopaedics of the Martini Hospital Groningen, the Netherlands. The orthopaedic surgeons who are participating in this study (N = 2) are experienced in performing the TT and AMP reconstruction technique. Patients in the TT group will be operated by [name]. Patients in the AMP group will be operated by [name]. They will perform all ACL reconstructions in the present study. Two independent radiologists will evaluate MRI outcomes. One independent investigator, not involved with enrolment or surgical procedure, will evaluate the functional and clinical outcome measurements. The study has been approved by a Medical Ethics Committee, and is also registered in the Netherlands Trial Registry [Reference: NTR5410].

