### Study sample

Patients suitable for enrolment in this study are candidates for primary unilateral ACL reconstruction with an age between 18 and 50 years and a proven ACL rupture confirmed by means of arthroscopy or MRI scan. Exclusion criteria are a history of previous surgery on the ipsilateral knee, re-rupture of the ipsilateral ACL graft, associated ligamentous injuries or meniscal tear of the ipsilateral knee, unhealthy or symptomatic contralateral knee by means of previous injury and/or surgery, contra-indications for MRI and a preference for one of the two surgical techniques and/or orthopaedic surgeon.

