**Fig. 1 Fig1:**
[figure not shown]
Flowchart of patient inclusion

A random allocation set of the type of ACL reconstruction technique will be generated by means of a computer. These allocations are then sealed in consecutively numbered opaque envelopes. Once the patient has given consent to be included in the trial, the ACL reconstruction technique is then randomly assigned by opening the next sealed envelope.

Patients will be blinded for the allocated surgical technique. Measurements and data-analysis will be performed by an independent investigator.

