## Conclusion

This paper describes the design of a randomized controlled trial on the SI of the graft after TT and AMP ACL reconstruction. The results of this study may clarify which surgical technique will reveal the best clinical, functional and quantitative MRI outcomes.

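### One surgeon performs every transtibial case and the other every anteromedial portal case, so the trial cannot separate the effect of technique from the effect of surgeon

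*Protocol article*

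**What the plan says.** The Study design section of the protocol article reports two participating surgeons: "The orthopaedic surgeons who are participating in this study (N = 2) are experienced in performing the TT and AMP reconstruction technique". It then gives each arm its own operator: "Patients in the TT group will be operated by [name]. Patients in the AMP group will be operated by [name". It adds: "They will perform all ACL reconstructions in the present study". The names are removed, but two surgeons, a separate operator sentence for each arm and no other operators leave one natural reading, which is one surgeon per arm.

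Under Randomization, technique is the randomised factor: "the ACL reconstruction technique is then randomly assigned by opening the next sealed envelope". The same section states: "Patients will be blinded for the allocated surgical technique". Patients hear about the study from their orthopaedic surgeon, and Study sample excludes those with "a preference for one of the two surgical techniques and/or orthopaedic surgeon".

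The aims concern technique. The Background predicts a lower signal with AMP because of better rotational stability, and Main study parameter/endpoint sets the objective as differences between the two techniques. The Conclusion says: "The results of this study may clarify which surgical technique will reveal the best clinical, functional and quantitative MRI outcomes". Statistical analysis compares the two groups by t-test, Mann–Whitney U or chi-square test. The Discussion lists other contributors to graft failure; the surgeon is not among them.

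**The concern.** Randomisation balances patients between the arms. It does not balance surgeons, because there is one on each side. Whatever is systematic about one operator's work is present in every patient of one arm and in none of the other. It enters the estimated difference in full and cannot be told apart from technique.

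The stake is the trial's central question. A significant difference in SIR could come from technique, surgeon or both, and a surgeon difference in the opposite direction could hide a real technique effect. The same applies to IKDC and KOOS.

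A secondary issue follows from the same arrangement. Since operator and allocation coincide, a patient who knows the operator and which technique that surgeon performs also knows the allocation.

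**Working it through.** **Inputs.** From Sample size calculation: difference 0.25, SD 0.21, power 90%, alpha 5% (sidedness not stated; two-sided assumed), 15 per group, 36 in total. From Study design: two surgeons, one per arm. The size of any surgeon effect is an assumption, because the documents give none.

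**1. The plan's own figure.** n per arm = 2 × (1.960 + 1.282)² × (0.21/0.25)² = 2 × 10.51 × 0.7056 = 14.8, so 15. Total: 30 × 1.2 = 36. Both reproduce. The calculation takes technique to be the only systematic difference between the arms.

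**2. Aliasing.** Let T be technique and S surgeon, each coded 0/1. In the model Y = a + bT + cS + error, T = S for every patient, so Y = a + (b + c)T + error. Only b + c can be estimated. The design matrix (intercept, T, S) has rank 2 of 3 at any sample size. If both surgeons work in both arms, the rank is 3 and b and c can be estimated separately.

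**3. Illustration with a random surgeon effect.** The standard error of the difference is 0.21 × √(2/15) = 0.0767. With between-surgeon SD τ, the variance of the difference becomes 0.0767² + 2τ². A nominal 5% test then has error 2 × [1 − Φ(1.96 × 0.0767 / √(0.0767² + 2τ²))]:

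| Assumed τ (SIR) | √(0.0767² + 2τ²) | Two-sided error |
|---|---|---|
| 0.03 | 0.0876 | 8.6% |
| 0.05 | 0.1043 | 15.0% |
| 0.10 | 0.1609 | 35.0% |

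With 0.21 as the within-surgeon SD, τ = 0.10 means an intraclass correlation of 0.01/(0.01 + 0.0441) = 0.18, so the last row is the far end of the range.

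**4. More patients.** The standard error shrinks with n but 2τ² does not, so the error rises. In the t-test version the critical value is divided by √(1 + n × ICC/(1 − ICC)). At an assumed ICC of 0.05 the error is 13.7% with 15 per arm and 51% with 150 per arm.

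**5. Illustration with a fixed surgeon difference** (15 per arm, noncentral t-test, no true technique effect). A surgeon difference in SIR of 0.05, 0.10, 0.15 or 0.20 gives a significant result in 9.7%, 24.2%, 47.2% or 71.2% of trials. Conversely, if technique truly lowers SIR by 0.25 and the surgeon difference works against it by 0.10, the net difference is 0.15 and power falls from 88.2% (exact t-test) to 47.2%.

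**6. Price of separating the effects.** With balanced allocation of both surgeons to both arms and a surgeon term, 30 evaluable patients give 88.1% power (27 degrees of freedom) against 88.2% unadjusted (28 degrees of freedom). With 36 evaluable it is 93.4%.

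**The case against.** **Operative steps are standardised.** Intervention and the two technique sections fix the same graft type, a notchplasty in every case, endobutton fixation on the femoral side, an interference screw on the tibial side and the same knee flexion at tibial fixation. This narrows operator differences and it stands. It does not remove them: finding the femoral insertion, setting the aimer angle and pretensioning still depend on the operator, and the Background calls AMP technically demanding.

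**The split may be deliberate.** A reader might infer that nothing required it, because the surgeons "are experienced in performing the TT and AMP reconstruction technique". That sentence can also mean that the pair covers both techniques between them. Matching operator to expertise is a recognised rationale, so a reason for the split cannot be ruled out. With a single surgeon per arm, however, it leaves the aliasing in place.

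**The blinding point can be overstated.** A reader might infer that patients know who operates and are therefore unblinded. The documents do not say so. The surgeon who informs a patient need not be the operator, since allocation follows consent, and nothing says patients are told which surgeon does which technique. An article may also leave the concealment of the operator to the full protocol. The preference exclusion shows at most that patients may be aware of more than one surgeon. What stands is a dependency, not a demonstrated failure, and it does not reach the primary MRI measure, which patients do not report.

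**The error rates rest on assumptions.** This is correct. They show direction and sensitivity and are not estimates for these two surgeons; in particular, 35% should not be quoted as the trial's error rate.

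**Conclusion.** The concern holds for the confounding. Under the article's own allocation of operators, technique and surgeon are completely aliased at any sample size. The trial estimates their combined effect and cannot answer its technique question as designed. This is a feature of the design that no analysis plan can repair. The conclusion rests only on the reading that each arm has one surgeon, which the Study design text supports.

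The size is unknown. Over an assumed between-surgeon SD of 0.03 to 0.10 in SIR, the two-sided 5% error would be about 9% to 35% at 15 per arm, and larger with more patients. The remark on blinding is conditional and concerns mainly KOOS.

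**What to change.** **Preferred, if each surgeon is proficient in both techniques, as Study design suggests.** Have both surgeons operate in both arms, stratify the random list by surgeon and include surgeon as a factor in the primary model. The cost is a protocol amendment, a new stratified set of envelopes and one degree of freedom (88.1% against 88.2% power at 30 evaluable). Proficiency in both should be confirmed first; otherwise unequal experience within a surgeon becomes a new source of bias. The result would still rest on two operators, and the change cannot reach patients already treated.

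**If the present arrangement stays, or patients have already been treated under it.** Restate the objective and conclusion as TT by one surgeon versus AMP by another, give the confounding as a limitation, and do not claim that the trial identifies the better technique. The cost is wording and a weaker conclusion.

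**In the fallback case,** also state how operator identity and the surgeon–technique pairing are kept from patients, or describe KOOS as not reliably blinded.

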### Study sample

Patients suitable for enrolment in this study are candidates for primary unilateral ACL reconstruction with an age between 18 and 50 years and a proven ACL rupture confirmed by means of arthroscopy or MRI scan. Exclusion criteria are a history of previous surgery on the ipsilateral knee, re-rupture of the ipsilateral ACL graft, associated ligamentous injuries or meniscal tear of the ipsilateral knee, unhealthy or symptomatic contralateral knee by means of previous injury and/or surgery, contra-indications for MRI and a preference for one of the two surgical techniques and/or orthopaedic surgeon.

### Intervention

The anaesthetic and analgesic protocol will be standardized. A first physical examination of the knee under anaesthesia and a diagnostic arthroscopy via an anterolateral portal are performed prior to any reconstruction. In both study groups, the same graft type will be used. The hamstring tendon graft will be harvested through a 6–7 cm long anterior central skin incision. A notchplasty will always be performed to avoid graft impingement.

#### Transtibial technique

An anterolateral and anteromedial portal are used. After removing the ACL remnants and performing a notchplasty, the tibial tunnel is prepared first. The remaining stump of the ACL is the major orientation guide. The tip of the tibial aimer is placed in the posterior fibers of the ACL footprint. With a 2.4 mm guide wire, the tibial plateau is protruded. The angle of the aimer is dependent on the length of the graft. To achieve a longer tibial tunnel, the angle of the tibial aimer is increased. The tibial tunnel is drilled with a cannulated drill bit that matches the graft diameter.

The femoral tunnel is prepared through the tibial tunnel with the knee flexed at 90 degrees. With the femoral aimer, the over the top position is determined with the offset hook. With a 2.7 mm guide wire, the lateral femoral cortex is penetrated. With an endoscopic cannulated drill bit, the femoral socket is created that matches the graft diameter. The depth of the femoral socket is regulated according to the desired insertion length. The depth is 9–10 mm greater than the desired graft insertion to allow the endobutton (Smith & Nephew, Memphis, Tenn) device to rotate. With a 4.5 mm endoscopic drill bit, a transfemoral channel is created allowing the endobutton device to pass. With an endobutton depth gauge the total length of the femoral condyle is measured. After graft preparation the endobutton CL device length is determined by the difference between the total femoral channel length hand the desired femoral graft insertion length. The graft is pulled through the tibial and femoral tunnel. The endobutton device is passing through the lateral femoral cortex. Afterwards, the graft is pulled back locking the endobutton on the lateral femoral cortex. After pretensioning the graft, the tibial part is fixed with a peek interference screw (Smith & Nephew, Memphis, Tenn) with the knee in 20 degrees of flexion.

#### Anteromedial portal technique

The femoral tunnel is created first using an accessory anteromedial portal. The insertion and remnants of the ACL on the femoral side are determined. When the soft tissue ACL remnants cannot be identified, the insertion is determined just below and inferior to the lateral intercondylar ridge. The femoral tunnel is prepared in the same way as in the TT technique working through the accessory anteromedial portal. During preparation of the femoral tunnel, the knee remains flexed to 120–130 degrees. After preparing the femoral tunnel, the tibial tunnel is created compared to the TT. Femoral side is fixed with the endobutton device, tibial side with a peek interference screw with the knee in 20 degrees of flexion.

### Main study parameter/endpoint

The primary objective of this study is to conduct a randomised controlled trial to determine differences in outcomes of both the AMP and TT ACL reconstruction technique by means of the MRI SIR of the ACL graft.

### Secondary study parameters/endpoints

Differences in functional and clinical outcomes between the AMP and TT ACL reconstruction technique will be assessed by means of the standardized physical examination and recorded by the use of the International Knee Documentation Committee (IKDC) Knee Examination Form [13]. The examination consist of Effusion, Passive Motion Deficit, Ligament Examination (Lachman and Pivot Shift), Compartmental Findings, Harvest Site Pathology and Functional Test (one leg hop test). Laxity measurements will be performed by using KT-2000 arthrometer testing (MedMetric, San Diego, CA). Power measurements of quadriceps and hamstring muscle groups will be performed by using Cybex isokinetic dynamometer (HUMAC). Patient’s will be classified in four groups depending on the lowest grade of the examination form.

Differences in patient-oriented outcomes between the AMP and TT ACL reconstruction technique will be assessed by the use of the Knee injury and Osteoarthritis Outcome Score (KOOS). The KOOS is a knee-specific instrument to assess the patients’ opinion in five subscales of Pain, other Symptoms, Function in daily living (ADL), Function in Sport and Recreation (Sport/Rec) and knee-related Quality of Life (QOL) with scores ranging from 0 (worst) to 100 (best) [14].

Besides differences between MRI SIR assessment with the current MRI protocol (PDWI and PDWI SPAIR imaging protocol) and the additional T2*WI gradient echo protocol. Integrity of cartilage, menisci, bone and other ligamentous structures will be assessed by using the Anterior Cruciate Ligament OsteoArthritis Score (ACLOAS) [15, 16].

